7.3.3 Other Antitumor Treatments

If the subject begins other antitumor treatments, non-fatal AEs should be reported until the start of new antitumor treatment. If death occurs after the end of study treatment but within the SAE reporting period, it must be reported promptly, regardless of whether the patient received other treatments.

7.3.4 Hospitalization

AEs leading to hospitalization or extended hospitalization during the clinical study should be considered SAEs, excluding hospitalization for non-medical purposes. Hospitalizations or extended hospitalizations unrelated to AE worsening are not considered SAEs. For example:

- Hospitalization for pre-existing conditions without new AE or worsening of existing conditions (e.g., laboratory abnormalities present before the trial).

- Hospitalization for administrative reasons (e.g., annual routine physical examinations).

- Hospitalization required by the clinical trial protocol (e.g., procedures required by the trial protocol).

- Elective hospitalization unrelated to AE worsening (e.g., elective cosmetic surgery).

- Pre-planned treatments or surgeries should be recorded in the overall trial protocol and/or each subject's baseline data.

- Hospitalization for blood product use only.

Diagnostic or therapeutic invasive procedures (e.g., surgery), non-invasive procedures should not be reported as AEs. However, if the condition leading to the procedure meets the definition of AE, it should be reported. For example, acute appendicitis occurring within the AE reporting period should be reported as an AE. Appendectomy performed as a result should be recorded as the treatment method for the AE.

7.3.5 SAE Reporting

During the trial, if an SAE occurs, whether it is an initial report or a follow-up report, the investigator must immediately complete the "Clinical Research SAE Report Form", sign, and date it, and report it to the Ethics Committee of the research institution. During the extended supply of the study drug after the study ends, any SAE must be reported within 24 hours after the investigator becoming aware of the SAE. All SAE information should be recorded in the SAE form. SAEs occurring within 90 days after the last administration must be reported. SAEs occurring after 90 days post-administration should generally not be reported unless they are suspected to be related to the study drug. SAEs should be recorded in detail, including symptoms, severity, time of occurrence, treatment time, measures taken, follow-up time and method, and outcome. If the investigator believes the SAE is unrelated to the study drug but potentially related to study conditions (e.g., discontinuation of the original treatment protocol or complications during the trial), the specific relationship should be described in the case report form's SAE page. If the intensity of the ongoing SAE or its relationship to the study drug changes, an SAE follow-up report should be sent to the investigator immediately. All SAEs should be followed up until recovery or stabilization of the condition.

Serious Adverse Event Contact Information

| **Unit** | **Contact Department** | **Reporting Method** | **Contact Information** |
| --- | --- | --- | --- |
| Ruijin Hospital | Ethics Committee | In-person | [contact] |

7.3.6 AEs of Special Interest

If any of the following AEs occur during the clinical trial, they must be reported to the investigator within 24 hours, even if they do not meet the SAE definition. If they also qualify as SAEs, the "Serious Adverse Event Report Form" must also be completed.

1. Infusion reactions of grade ≥ 3 (even if not dose-limiting toxicity, DLT).
2. Diarrhea/colitis, uveitis, or interstitial pneumonia of grade ≥ 2.
3. Other immune-related AEs of grade ≥ 3.
4. Any potential Hy's Law event (ALT/AST > 3× ULN, TBIL > 2× ULN without other related causes).
5. Any grade of GVHD.

7.3.7 Infusion Reactions

For potential infusion and/or allergic reactions, especially acute infusion reactions, the investigator needs to closely monitor throughout the study. Generally, no premedication is required before UCB infusion. According to published data,^15^ immediate-type allergic reactions/anaphylaxis are most likely to occur within 24 hours after infusion. If they occur, the infusion should be slowed or interrupted, clinical supportive treatment should be given, and premedication should be administered before the next infusion. Possible allergic reactions include fever, chills, tremors, headache, rash, itching, arthralgia, hypotension or hypertension, or bronchospasm. All grade 3 or 4 infusion reactions, whether they meet DLT criteria or not, should be reported according to SAE procedures. The management of allergic reactions should follow the medical practices and guidelines of the research institution. The following are suggested guidelines for managing infusion reactions.

7.3.8 Follow-up of AEs/SAEs

All SAEs and drug-related AEs should be followed up until they disappear, return to baseline level or ≤ grade 1, the condition stabilizes, or an explanation is obtained (e.g., loss to follow-up, death). At each follow-up, the investigator should inquire about any AE/SAE occurrences since the last follow-up, and whether any new AE/SAE has occurred, recording relevant updated information, including outcomes.

7.4 Common Adverse Reactions of Decitabine

1) Hematologic Toxicity:

- Neutropenia (low neutrophil count)

- Thrombocytopenia (low platelet count)

- Anemia (low red blood cell count)

- Leukopenia (low white blood cell count)

- Febrile neutropenia (fever with low neutrophil count)

2) Infections:

- Increased susceptibility to infections, including pneumonia, sepsis, and upper respiratory infections

3) Gastrointestinal:

- Nausea

- Vomiting

- Diarrhea

- Constipation

- Abdominal pain

4) General:

- Fatigue

- Fever

- Weakness

- Edema (swelling)

5) Hepatic:

- Elevated liver enzymes (ALT, AST)

- Hyperbilirubinemia (elevated bilirubin levels)

6) Cardiovascular:

- Hypotension (low blood pressure)

7) Dermatologic:

- Rash

- Petechiae (small red or purple spots on the body)

8) Respiratory:

- Cough

- Dyspnea (difficulty breathing)

9) Musculoskeletal:

- Arthralgia (joint pain)

- Myalgia (muscle pain)

10) Renal:

- Elevated serum creatinine

11) Neurologic:

- Headache

- Dizziness

7.5 Common Adverse Reactions of Cytarabine

1) Hematologic Toxicity:

- Neutropenia (low neutrophil count)

- Thrombocytopenia (low platelet count)

- Anemia (low red blood cell count)

- Leukopenia (low white blood cell count)

2) Gastrointestinal:

- Nausea

- Vomiting

- Diarrhea

- Stomatitis (inflammation of the mouth)

- Esophagitis (inflammation of the esophagus)

- Anorexia (loss of appetite)

3) General:

- Fatigue

- Fever

- Malaise (general discomfort)

4) Hepatic:

- Elevated liver enzymes (ALT, AST)

- Hyperbilirubinemia (elevated bilirubin levels)

- Hepatotoxicity

5) Dermatologic:

- Rash

- Erythema (redness of the skin)

- Alopecia (hair loss)

- Dermatitis (inflammation of the skin)

6) Neurologic:

- Cerebellar toxicity (manifesting as ataxia, nystagmus, dysarthria)

- Peripheral neuropathy (nerve damage causing numbness or tingling)

- Headache

- Dizziness

7) Respiratory:

- Pneumonitis (inflammation of the lung tissue)

- Pulmonary edema (fluid in the lungs)

- Dyspnea (difficulty breathing)

8) Ocular:

- Conjunctivitis (inflammation of the eye)

- Keratitis (inflammation of the cornea)

9) Renal:

- Elevated serum creatinine

- Hematuria (blood in the urine)

10) Infections:

- Increased risk of bacterial, fungal, and viral infections due to immunosuppression

11) Other:

- Pain at the injection site

- Localized tissue necrosis (if extravasation occurs)

7.6 Management of Common Adverse Reactions Related to Drugs

7.6.1 Bone Marrow Suppression

1) Leukopenia

- Indications for G-CSF in the treatment of febrile neutropenia:

Sepsis, age > 65, severe neutropenia (absolute neutrophil count < 100/mcl), expected duration of neutropenia exceeding 10 days, pneumonia or other clinically documented infections, invasive fungal infections, hospitalization due to fever, history of febrile neutropenia. Some leukemia chemotherapy regimens require prophylactic G-CSF to ensure the smooth administration of chemotherapy doses and schedules. The use of prophylactic G-CSF is decided by the investigator based on the patient's actual condition.

- G-CSF Administration Method:

Pegylated G-CSF: Therapeutic or prophylactic use: Single use per cycle. Dosage: 6 mg for body weight > 45 kg; 3 mg for body weight ≤ 45 kg, administered the day after chemotherapy ends.

- Management of Febrile Neutropenia:

a). Assess infection risk and resistance, and initiate empirical antibiotics immediately.

b). Antibacterial treatment should continue throughout the neutropenia period until ANC > 0.5×10⁹/L.

c). Initial empirical antibiotic therapy aims to reduce serious complications and mortality from bacterial infections. Accurate microbiological culture results are essential.

d). Choice of empirical antibiotic therapy should consider the patient's comprehensive evaluation (risk stratification, infection site, organ function, resistance risk factors), bacteria (local and institutional epidemiology and resistance surveillance data), and the antibiotic itself (broad spectrum, pharmacokinetics/pharmacodynamics, side effects). Attention should be paid to overlapping side effects with drugs used to treat the primary disease (e.g., hematologic tumor chemotherapy drugs, immunosuppressants).

e). Low-risk patients: Initial treatment can be outpatient with the options of oral or intravenous empirical antibiotics. Combined therapy with oral ciprofloxacin, amoxicillin/clavulanate, levofloxacin, or moxifloxacin is recommended.

f). High-risk patients: Immediate hospitalization. For patients with mild conditions, a progressive strategy is taken, initially using broad-spectrum antibiotics such as cephalosporins to reduce increased bacterial resistance due to antibiotic misuse; for patients with severe conditions, a regressive strategy is taken to improve prognosis.

2) Thrombocytopenia

- Chemotherapy-Induced Thrombocytopenia (CIT): Refers to the inhibition of bone marrow, especially megakaryocytes, by chemotherapy drugs, causing peripheral blood platelet counts to drop below 100×10⁹/L.

a). Treatment of CIT: Platelet transfusion, administration of platelet growth factors such as recombinant human interleukin-11 (rhIL-11) or recombinant human thrombopoietin (TPO).

b). rhIL-11 Administration: rhIL-11 should be used when platelet counts are 25~75×10⁹/L. Recommended dose is 25~50 µg/kg, subcutaneously, once daily for at least 7-10 days. Discontinue when platelet count reaches 75×10⁹/L.

c). rhTPO Administration: If chemotherapy drugs are expected to cause thrombocytopenia and induce bleeding, requiring increased platelet counts, administer subcutaneously 6-24 hours after chemotherapy ends, at a dose of 300 U/kg daily for 7-10 days. Regularly monitor complete blood counts, usually every other day, and discontinue when platelet count reaches 75×10⁹/L.

3) Anemia

- Cancer-Related Anemia (CRA): Refers to anemia occurring during cancer progression and treatment. Laboratory tests are needed to determine the cause. Treatment principles are as follows:

a). Non-Chemotherapy-Related Anemia: Provide targeted treatment for different causes.

Nutritional anemia: Supplement with iron, folic acid, and vitamin B12; autoimmune anemia: Treat with corticosteroids (if not contraindicated); tumor-related inflammation or chemotherapy-induced bone marrow suppression: Evaluate the risk-benefit of treatment and decide whether to use blood transfusions or erythropoiesis-stimulating agents (EPO).

b). Red Blood Cell Transfusion: Quickly increases hemoglobin (HGB) and hematocrit (HCT). In China, blood transfusion is recommended when HGB < 6 g/dL. Consensus on transfusion in China: Severe or above anemia patients; moderate anemia with severe symptoms; EPO ineffective patients.

c). EPO: Takes weeks to stimulate HGB elevation but is effective in maintaining HGB at an appropriate target level. For leukemia chemotherapy-induced anemia, consider using EPO after evaluating the risk of thrombosis.

d). Parenteral Iron Supplements: Treat iron-deficiency anemia (transferrin saturation < 15%, serum ferritin < 30 ng/mL) with oral or intravenous iron supplements without simultaneous EPO. Low-molecular-weight dextran iron, ferric gluconate, or ferric sucrose are recommended due to fewer side effects.

7.6.2 Gastrointestinal Reactions

Chemotherapy-Induced Nausea and Vomiting (CINV): Common adverse reactions during cancer treatment, significantly affecting patients' quality of life and potentially leading to reduced or discontinued chemotherapy regimens.

- Anticancer drugs can be classified into high, moderate, low, and minimal emetogenic risk levels, meaning the vomiting incidence without prophylactic treatment is > 90%, 30%-90%, 10%-30%, and < 10%, respectively.

- Prophylactic Antiemetics: This protocol recommends combined use of neurokinin-1 (NK-1) receptor antagonists (aprepitant), 5-HT3 receptor antagonists, etc., before chemotherapy.

- Delayed Antiemesis: For severe vomiting after chemotherapy, administer metoclopramide 20 mg intramuscularly twice daily, oral 5-HT3 receptor antagonists (e.g., ondansetron orally disintegrating tablets), or oral NK-1 receptor antagonists (e.g., aprepitant) post-chemotherapy for antiemesis.

7.6.3 GVHD

Routine monitoring of peripheral blood microchimerism is performed after treatment, and if the chimerism rate exceeds 5%, GVHD treatment should be initiated immediately.

1). First-line Treatment:

- Corticosteroids: Methylprednisolone 1-2 mg/kg/day or equivalent dose for 2-3 weeks.

- Calcineurin Inhibitors: Such as cyclosporine A and tacrolimus.

2). Second-line Treatment (for refractory or dependent cases):

- Antithymocyte Globulin: Such as rabbit antithymocyte globulin (ATG).

- Monoclonal Antibodies: Such as anti-CD25, anti-CD52, and anti-TNF-α.

- mTOR Inhibitors: Such as sirolimus.

- Mesenchymal Stem Cell (MSC) Infusion.

- Ruxolitinib: A JAK1/2 inhibitor.

- Extracorporeal Photopheresis (ECP).

3). Supportive Treatment:

- Skin: Maintain cleanliness and prevent infection.

- Liver: Hepatoprotective treatment, discontinue hepatotoxic drugs if necessary.

- Gastrointestinal Tract: Correct electrolyte imbalances, monitor for bleeding, and withhold food if necessary.

4). Close monitoring of organ function changes, prevention and treatment of infections, and other complications. Transfer to the bone marrow transplant unit or ICU as needed.

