5.2 Study Treatment

Consolidation Therapy:

- Two cycles of 15 mg/m^2^ low dose intravenous decitabine (DAC) over 4h per day for consecutive 5 days (day 1-5), 1.0 g/m^2^ intermediate-dose cytarabine (Ara-C) at q12h for consecutive 2 days (day 6-7), combined with one unit UCB infusion on day 9.

- No immunosuppression was given as prophylaxis for GVHD, unless acute GVHD (aGVHD) was documented or clinically diagnosed.

Selection of UCB:

- High-resolution Human Leukocyte Antigen (HLA) typing for HLA-A, B, and DR loci was performed in all enrolled patients.

- The UCB units were obtained from the cord blood bank at the China Shandong Cord Blood Bank Network if they met the following criteria:

a). Serologically matched of four or five of six HLAs.

b). Contained at least 3 × 10⁷ nucleated cells/kg of recipient body weight before freezing.

Maintenance Therapy:

- Decitabine 15 mg/m² for 5 days, every 28-day cycle.

OR

- Azacitidine 75 mg/m² for 7 days, every 28-day cycle.

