5.3 Evaluation and Examination During Treatment

1. After completing each treatment cycle, patients were required to have a complete blood count examination every 3 days and coagulation function, liver, and kidney function examinations weekly. The main indicator values were documented during the process.
2. Physical examination, toxicity assessment, and pre-chemotherapy assessment (including complete blood count, biochemical routine, coagulation function, EBV-DNA, serum amylase, urine protein and urinalysis, stool routine + occult blood, serum β2-MG, thyroid function, six items of cardiac function, electrocardiogram, echocardiography, and for hepatitis B or C patients, HBV-DNA and HCV-RNA testing).
3. Chimerism Analysis: on the day 7 after UCB infusion, peripheral blood cells were collected from all patients and assessed for chimerism using standard cytogenetic and a semi-quantitative polymerase chain reaction based assay of short tandem repeats with the sensitivity of 1%.

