5.5 Follow-up Evaluation

Schedules:

- Post-UCB treatment on days 14, 30, and 60.

- Before each chemotherapy session and before and after each maintenance treatment during the treatment period.

- After the end of treatment, follow-up assessments were performed monthly in the first year, and every three months thereafter.

Testing Items:

- Bone marrow aspiration smear, MRD, bone marrow chimerism detection.

- Chromosome testing was required after consolidation and maintenance therapy.

- If there was any disease recurrence detected by bone marrow cytology at any time during the treatment, the treatment will be deemed ineffective. Then the patient will be withdrawn from this study and enter the trials for relapsed and refractory AML treatment.

- If bone marrow chimerism > 30% at any time during treatment, donor engraftment will be considered, and the patient will be withdrawn from the clinical trial and receive anti-rejection treatment.

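### Protocol sections 5.2 and 7.6.3 set different triggers for immunosuppression, so a patient above 5% chimerism without clinical GVHD falls under conflicting instructions

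*Protocol*

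**What the plan says.** Four sections of the protocol bear on this point.

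- **Section 5.2 (Study Treatment):** "No immunosuppression was given as prophylaxis for GVHD, unless acute GVHD (aGVHD) was documented or clinically diagnosed". No chimerism value appears.
- **Section 7.6.3 (GVHD):** The trigger reads "if the chimerism rate exceeds 5%, GVHD treatment should be initiated immediately", in a sentence that opens with "Routine monitoring of peripheral blood microchimerism is performed after treatment". The first-line list below it has corticosteroids and then "Calcineurin Inhibitors: Such as cyclosporine A and tacrolimus". No clinical sign of GVHD is required.
- **Section 5.5 (Follow-up Evaluation):** The trigger reads "If bone marrow chimerism > 30% at any time during treatment, donor engraftment will be considered". The consequence attached to that trigger is that "the patient will be withdrawn from the clinical trial and receive anti-rejection treatment". The compartment, threshold and action all differ from those in 7.6.3.
- **Section 5.3 (Evaluation and Examination During Treatment):** "on the day 7 after UCB infusion, peripheral blood cells were collected from all patients and assessed for chimerism". The assay is semi-quantitative, with a stated sensitivity of 1%.

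Section 7.3.6 makes GVHD of any grade an adverse event of special interest. Section 9.2 removes patients with protocol violations from the per-protocol set and uses both that set and the full analysis set for efficacy.

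**The concern.** Sections 5.2 and 7.6.3 do not agree on what starts immunosuppression. In one it is a diagnosis, in the other a laboratory value. The two part company for a patient whose peripheral chimerism is above 5% and who has no sign of GVHD.

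Three quantities depend on which section was followed:

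- **GVHD incidence.** The protocol does not say whether a patient given GVHD treatment for chimerism alone counts as a GVHD case. Counting such patients raises the incidence. Early treatment might also keep clinical GVHD from appearing, which would lower it.
- **Exposure to immunosuppressants.** Use for diagnosed disease and use on a laboratory value would be added together unless they are told apart.
- **Per-protocol membership.** Either way of handling the patient departs from one of the two sections.

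A related matter is the withdrawal rule in section 5.5. Overall survival is the primary endpoint, and the protocol does not say that survival follow-up continues after a withdrawal for chimerism above 30%.

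**Working it through.** The protocol gives no figure to reproduce here, so the check sets the rules side by side and runs patient types through them.

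**Inputs**

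| Section | Compartment | Trigger | Action |
|---|---|---|---|
| 5.2 | none named | acute GVHD, documented or clinically diagnosed | lifts the bar on immunosuppression |
| 7.6.3 | peripheral blood | chimerism above 5% | GVHD treatment at once |
| 5.5 | bone marrow | chimerism above 30% | withdrawal and anti-rejection treatment |

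Section 5.3 supplies the peripheral test: day 7 after infusion, all patients, sensitivity 1%. The 5% trigger is five times the detection limit, and the test does not depend on symptoms, so a patient without signs can meet the trigger.

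**Patient types**

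1. *Peripheral chimerism above 5%, no GVHD documented or diagnosed.* Section 7.6.3 starts treatment at once. Under 5.2 the exception that permits immunosuppression is not met. The instructions conflict.
2. *Peripheral chimerism above 5%, GVHD clinically diagnosed.* Both sections allow treatment. No conflict.
3. *Peripheral chimerism of 5% or less, GVHD clinically diagnosed.* The exception in 5.2 is met. The trigger in 7.6.3 is not, but that section does not forbid treatment. No conflict.
4. *Bone marrow chimerism of 30% or less.* Section 5.5 triggers nothing, while 7.6.3 may already apply through peripheral blood. Both can be followed.
5. *Bone marrow chimerism above 30%.* Section 5.5 adds withdrawal and a treatment that it does not define; 7.6.3 is silent on withdrawal. Both can be followed, but their relation is not stated.

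Only type 1 is a direct conflict. Types 4 and 5 show an unlinked rule.

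**Per-protocol membership.** A type 1 patient who is left untreated departs from 7.6.3, and one who is treated departs from 5.2. Applied literally, the exclusion of protocol violators in section 9.2 could catch the patient either way.

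**Withdrawal and survival.** Section 2.2.1 censors survival at last follow-up for patients known to be alive. The definition of the full analysis set in 9.2 gives no reason to drop a patient withdrawn for chimerism, but the length of that patient's survival follow-up is left open.

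**Scale.** Section 15 gives 51 enrolled. If *k* patients change GVHD status with the rule applied, incidence moves by *k*/51. The protocol does not give *k*, so the values below are assumptions:

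- *k* = 0: no change
- *k* = 1: 1/51 = 2.0 percentage points
- *k* = 3: 3/51 = 5.9 points
- *k* = 5: 5/51 = 9.8 points

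The denominator in section 7.2.2 is the number evaluated for safety. If that is below 51, each step is slightly larger.

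**The case against.** The best defence is that 5.2 speaks of prophylaxis and 7.6.3 of treatment, so the two govern different things. The word documented in 5.2, set beside clinically diagnosed, might also be meant to take in a laboratory finding. This softens the conflict but does not remove it. Treating a patient who has no GVHD is pre-emptive in substance, and no section says that chimerism above 5% is documented GVHD.

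The other objections limit how far the point reaches, and they stand.

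- *A reader might infer a three-way contradiction with section 5.5.* The text does not support that. Section 5.5 concerns another compartment and a higher threshold, and a site can obey it together with 7.6.3. The fault is that the rules are not linked.
- *A reader might infer that 5.3 contradicts the routine monitoring in 7.6.3.* It does not. Section 5.3 fixes day 7 without excluding other days, and if a unit is given in each of the two cycles there would be more than one test. Day 7 is only the one peripheral time point that is stated; chimerism in the 5.5 schedule is bone marrow. Monitoring is underspecified, not contradicted.
- *A reader might infer that GVHD incidence cannot be interpreted.* Section 7.3.6 collects GVHD of any grade whatever prompted treatment, and section 7.2 requires symptoms, severity and measures taken for each event. The records should show whether signs were present.
- *A reader might infer an effect of the extra immunosuppression on relapse or survival.* The protocol offers nothing to support or measure one.

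**Conclusion.** The point holds as one direct conflict, between sections 5.2 and 7.6.3, for patients above 5% peripheral chimerism without documented or clinically diagnosed GVHD. Beside it stand an unlinked bone marrow rule in 5.5 and a peripheral monitoring schedule with a single stated time point in 5.3.

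GVHD incidence, immunosuppressant exposure and per-protocol membership are ambiguous as a result, though they should be recoverable from the records. GVHD is not a separately named endpoint, so the incidence problem sits within the safety reporting; the per-protocol question reaches a secondary efficacy population. The size is about 2.0 percentage points of GVHD incidence per affected patient, for an unknown number that could be zero.

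The conclusion rests on two readings: that the 5% threshold refers to peripheral blood, as its sentence suggests, and that a chimerism value alone is not documented GVHD, since no section says that it is. It should be corrected, but it does not undermine the primary analysis.

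**What to change.** The responsible clinicians and the ethics committee should reconcile sections 5.2, 5.3, 5.5 and 7.6.3 on compartment, test times, trigger and action. Which rule is right is a clinical matter and is left to them.

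Section 15 shows enrolment closed on 12 February 2022 and last follow-up on 31 March 2023, so a change of text cannot alter how patients were handled. The report should therefore:

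1. State which rule was applied in practice, and whether that changed during the trial.
2. Classify each use of immunosuppression, from existing records, as following documented or clinically diagnosed GVHD or following chimerism alone.
3. Report the two groups separately, so that no case definition is imposed after the event.
4. State how patients above 5% without GVHD were assigned to the per-protocol set.
5. Keep patients withdrawn for chimerism above 30% in the full analysis set and in overall survival follow-up, and say how many there were.

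The cost is a small record review in at most 51 patients and a few lines of text. No new data collection is needed if the adverse event records were kept as section 7.2 requires.
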